## Abstract

**Background:**

Improving the lifestyle of overweight and obese adults is of increasing interest in view of its role in several chronic diseases. Interventions aiming at overweight or weight-related chronic diseases suffer from high drop-out rates. It has been suggested that Motivational Interviewing and more frequent and more patient-specific coaching could decrease the drop-out rate. 'BeweegKuur' is a multidisciplinary lifestyle intervention which offers three programmes for overweight persons. The effectiveness and the cost-effectiveness of intensively guided programmes, such as the 'supervised exercise programme' of 'BeweegKuur', for patients with high weight-related health risk, remain to be assessed. Our randomized controlled trial compares the expenses and effects of the 'supervised exercise programme' with those of the less intensively supervised 'start-up exercise programme'.

**Methods/Design:**

The one-year intervention period involves coaching by a lifestyle advisor, a physiotherapist and a dietician, coordinated by general practitioners (GPs). The participating GP practices have been allocated to the interventions, which differ only in terms of the amount of coaching offered by the physiotherapist. Whereas the 'start-up exercise programme' includes several consultations with physiotherapists to identify barriers hampering independent exercising, the 'supervised exercise programme' includes more sessions with a physiotherapist, involving exercise under supervision. The main goal is transfer to local exercise facilities. The main outcome of the study will be the participants' physical activity at the end of the one-year intervention period and after one year of follow-up. Secondary outcomes are dietary habits, health risk, physical fitness and functional capacity. The economic evaluation will consist of a cost-effectiveness analysis and a cost-utility analysis. The primary outcome measures for the economic evaluation will be the physical activity and the number of quality-adjusted life years. Costs will be assessed from a societal perspective with a time horizon of two years. Additionally, a process evaluation will be used to evaluate the performance of the intervention and the participants' evaluation of the intervention.

**Discussion:**

This study is expected to provide information regarding the additional costs and effects of the 'supervised exercise programme' in adults with very high weight-related health risk.

**Trial registration number:**

ISRCTN: ISRCTN46574304

## Background

The increasing prevalence of overweight and obesity is a major problem in Western countries. People who are overweight are at higher risk of developing type 2 diabetes mellitus, cardiovascular disease and certain types of cancer [1]. In addition, their health-related quality of life decreases due to the overweight as such as well as to related comorbidities [2]. In the Netherlands, 42% of women and 53% of men are overweight (BMI > 25 kg/m^2^), of which 12% and 11% respectively are obese (BMI > 30 kg/m^2^) [3]. Health care expenses caused by overweight in the Netherlands amounted to half a billion Euros in 1999 [4].

Not only overweight but also physical inactivity have been associated with chronic diseases like type 2 diabetes and cardiovascular disease [5-7]. Intervening in people's lifestyles could help decrease the severity of chronic diseases and the risk of developing them. Combined lifestyle interventions aimed at increasing physical activity and improving dietary behaviour have been shown to have positive effects on metabolic and cardiovascular risk factors (e.g. weight, waist circumference, fat mass, HDL-cholesterol and triglyceride values and blood pressure) in persons at risk for developing chronic diseases [8-13], as well as in patients who have already developed type 2 diabetes [14-17]. Beneficial effects are still evident after a follow-up period of several years [7,8].

Recently, a multidisciplinary combined lifestyle intervention for type 2 diabetes patients, called 'BeweegKuur', has been developed by the Netherlands Institute for Sport and Physical Activity (NISB) [18,19]. Its target population currently also comprises overweight and obese patients. The primary goal of the 'BeweegKuur' interventions is to improve physical activity and dietary behaviour and thereby decrease health risks. A recent study reported, however, that the adherence to exercise intervention programmes varies widely, from 10% to 80% [20]. The main causes of drop-out are exercise-related injuries and motivational factors [14]. It seems likely, therefore, that the use of Motivational Interviewing [20,21] and the individualization of the 'BeweegKuur' programmes would result in lower drop-out rates. In addition, it has been proposed to have practice nurses play a key role in the adoption of long-term behavioural change by providing this individualized guidance in the primary health care setting [9,22]. In the 'BeweegKuur' programmes, the participant's behavioural change is supported by a team consisting of a general practitioner (GP), a lifestyle advisor (LSA), a physiotherapist and a dietician. The LSA (who may be a practice nurse or a physiotherapist) has the key role in this multidisciplinary team and offers wide-ranging lifestyle counselling aimed at promoting physical activity, improving diet and reducing psychological barriers by means of Motivational Interviewing [21]. A physiotherapist provides coaching for physical activity to enable participants to transfer to local exercise facilities, and a dietician provides advice on dietary improvement. The use of the 'BeweegKuur' programmes in primary care has proved to be feasible, as health care providers as well as participants are very positive about the programmes after having implemented it [23,24].

Care providers using 'BeweegKuur' offer three programmes, differing in the amount of support. The 'independent exercise programme' is intended for overweight and obese individuals without comorbidities, while the 'start-up exercise programme' and the 'supervised exercise programme' are both intended for adults with overweight or obesity who suffer from comorbidities or are morbidly obese. An earlier study showed that the amount of support required to achieve lifestyle changes increases with the severity of overweight and the presence of comorbidities [9]. Additionally, the number of feedback sessions is believed to be positively related to programme adherence [20]. Hence, the 'supervised exercise programme' involves more coaching by the physiotherapist.

Less intensively supervised programmes have been shown to be effective and cost-effective for people with type 2 diabetes or an increased risk of developing type 2 diabetes [8,13,17]. The effectiveness and cost-effectiveness of intensively supervised programmes for a population with very high weight-related health risk remain to be studied. Therefore, our randomized controlled trial aims to evaluate the effects of the 'supervised exercise programme', in terms of the amount of physical activity and related health risks, and its cost-effectiveness, compared to those of the 'start-up exercise programme', for this population. The time horizon of the study will be two years. The economic evaluation will involve cost-effectiveness and cost-utility analyses from a societal perspective. In addition, a process evaluation is planned.

## Methods/Design

### Study design

The present study is a clustered, multi-centre, randomized controlled trial evaluating the effectiveness and cost-effectiveness of the 'supervised exercise programme' versus the less intensively supervised 'start-up exercise programme' for patients with very high weight-related health risk. Thirty Dutch GP practices, each collaborating with a practice nurse, a physiotherapist and a dietician, have been randomly assigned to the control or experimental condition. In experimental practices, participants will take part in the 'supervised exercise programme', while participants in a control practice will take part in the 'start-up exercise programme'. Clinical outcome measurements take place at baseline, after 12 months (the end of the intervention period) and after 24 months (Figure 1). In addition, self-administered questionnaires comprising cost-, effect- and process-related outcome measures will be sent to the participants every three months.

**Figure 1 F1:**
[figure not shown]
**Flowchart of the 'BeweegKuur' randomized controlled trial and measurements**. A. Health care utilisation and productivity losses, EQ5-D and process items in questionnaire every three months; B. Clinical outcomes measured in questionnaire every six months; C. Clinical outcome measurements performed every year. Table 2 shows outcomes in each category. T0-T24 represent moments of measurement. T0 = Baseline; T3 = Three months after baseline; T6 = Six months after baseline; ...; T24 = 24 months after baseline.

This study is approved by the Medical Ethics Committee of the Maastricht University Medical Centre and is registered with Current Controlled Trials (ISRCTN46574304). The study is funded by The Netherlands Organization for Health Research and Development (ZonMW; project number: 123000002).

### Randomization

To reduce the risk of contamination between participants, and the risk of bias at the level of the professionals involved, entire practices have been allocated to the control or experimental condition. Prior to randomization, all practices have been matched pair wise based on size and location in an urban or rural area, to create two equivalent samples of 15 practices. In each pair, one practice has been randomized to the control condition, while the other was randomized to the experimental condition. To reduce the risk of contamination within a region, practices in the same region were allocated to the same condition as the first practice in that region that was randomized.

### Participants

Inclusion of participants started in July 2010. Inclusion criteria are (1) being overweight or obese (BMI 25-35 kg/m^2^) combined with the following serious related comorbidities: sleep apnoea, arthritis, cardiovascular disease and/or type 2 diabetes; or (2) being morbidly obese (BMI 35-40 kg/m^2^) but without these related serious comorbidities. In addition, participants should currently fail to meet the Dutch norm for healthy physical activity (30 minutes of moderate to vigorous physical activity on at least 5 days a week), have to be sufficiently motivated to change their physical activity level and dietary behaviour (to be judged subjectively by the LSA during intake) and have to give their informed consent.

Participants are being included via GPs, practice nurses and physiotherapists. The GP, practice nurse or physiotherapist selects patients by discussing the intervention during a consultation. However, they can also recruit patients actively (e.g. by searching the health care provider's records). The LSA screens the patients for eligibility. Exclusion criteria are serious mobility limitations precluding participation in the intervention programme, such as severe cardiac failure, serious angina pectoris and rheumatoid arthritis. Pregnancy is also an exclusion criterion. The GP decides whether patients should be excluded.

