### Blinding

Although it is not possible to blind the professionals, randomization at the level of GP practices decreases the risk of contamination among the professionals. Participants are not aware of the allocation of their practice to the experimental or control condition.

To identify effects of observer bias, clinical measurements that might be affected (Åstrand test, Valk neuropathy test, body composition, hand grip strength and Timed Up and Go Test) will be repeated by a researcher blinded for the randomization of the practices and the baseline characteristics of the participants. Repeated measurements will be done for 20 participants in five randomly chosen control and five randomly chosen experimental practices.

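### Unblinded practice staff choose and judge participants after practices are allocated, so the arms can differ at entry despite randomisation; size and direction are unknown

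*Protocol article*

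**What the plan says.** Allocation is described as completed. Under Study design, practices "have been randomly assigned to the control or experimental condition"; under Randomization, "entire practices have been allocated to the control or experimental condition". Recruitment is described as continuing. Under Participants, inclusion started in July 2010 and "Participants are being included via GPs, practice nurses and physiotherapists".

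The same section sets out how patients enter:

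- **Approach.** "The GP, practice nurse or physiotherapist selects patients by discussing the intervention during a consultation", and "they can also recruit patients actively (e.g. by searching the health care provider's records"). No order or common procedure is given.
- **Screening.** "The LSA screens the patients for eligibility". Among the criteria, patients "have to be sufficiently motivated to change their physical activity level and dietary behaviour (to be judged subjectively by the LSA during intake").
- **Exclusion.** This is the GP's decision. The grounds are pregnancy and mobility problems too serious for the patient to take part in the programme.

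The Background says that the lifestyle advisor (LSA) may be a practice nurse or a physiotherapist. The Blinding section concedes that "it is not possible to blind the professionals", and adds that participants do not know their practice's allocation. It presents practice-level randomisation as protection against contamination; the Randomization section also cites bias among the professionals.

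**The concern.** Randomising practices makes the practices comparable. It makes the patients comparable only if they are identified before allocation, or by people or rules that do not depend on it. Here each recruiter knows in advance which arm every patient will join.

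The article itself supplies reasons why this could matter:

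- Table 1 sets 26 to 34 supervised sessions against no scheduled supervised block in the control arm, which has six physiotherapist consultations in all. The Background says that patients with more severe overweight or comorbidity need more support. Staff could reasonably picture different patients as suitable for each programme.
- The mobility exclusion refers to taking part in the programme, and the programme differs by arm.
- The Background names motivational factors as a main cause of drop-out, so the subjectively judged criterion is prognostic on the article's own account.

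A resulting difference would act directly on the primary outcome, physical activity. A larger sample does not remove it, and intention-to-treat preserves the groups as recruited, including any imbalance at entry.

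**Working it through.** **1. Sequence and discretion.** Allocation is in the perfect tense and inclusion in the present continuous. No randomisation date is given. The wording therefore supports allocation before at least the ongoing recruitment, and says nothing certain about the first participants. Discretion enters at three steps: approach, motivation and exclusion. Unblinded staff of the allocated practice take all three.

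**2. Do the stated safeguards reach it?**

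| Safeguard | What it does | Prevents selective entry? |
|---|---|---|
| Pair matching on practice size and urban/rural setting | Balances practices | No: patients are chosen later |
| Participants unaware of allocation | Limits self-selection by patients | No: staff still choose |
| Blinded repeat measurements in a subsample | Detects observer bias | No |
| Intention-to-treat | Keeps the recruited groups intact | No |
| BMI, comorbidity and activity-norm criteria | Restrict who can enter | In part |

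**3. The plan's own sample size.** Inputs from Sample size: difference 50 min/week, SD 120, two-sided 5%, power 80%, drop-out 30%, intra-cluster correlation 0.05, 20 per practice.

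- Per arm: 2 × (120 × (1.96 + 0.842) / 50)² = 90.4, so 91. This reproduces the stated figure.
- With drop-out as the article applies it: 91 × 1.3 = 118.3, so 119 per arm and 238 in total.
- Design effect: 1 + 19 × 0.05 = 1.95. Then 238 × 1.95 = 464.1, and 464.1 / 20 = 23.2, rounded up to the stated 24 practices.

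**4. Standard error for the illustration.** Take 12 practices per arm with 20 × 0.7 = 14 completers each, or 168 per arm. The design effect is 1 + 13 × 0.05 = 1.65.

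SE = √(2 × 120² × 1.65 / 168) = 16.8 min/week.

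**5. Effect of an assumed entry-driven shift b.** The values of b are assumptions; the article gives none. Error with no true effect: P(|Z + b/SE| > 1.96). Power for a true 50 minutes when the shift works against the supervised arm: Φ((50 − b)/SE − 1.96). With b = 0 the power is 84%.

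| b (min/week) | Two-sided error | Power, shift against supervised arm |
|---|---|---|
| 5 | 6.0% | 76% |
| 10 | 9.1% | 66% |
| 15 | 14.5% | 55% |
| 20 | 22.1% | 43% |
| 25 | 31.8% | 32% |

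Worked for b = 15: 15 / 16.8 = 0.89, giving an error of 14.5%. For power, (50 − 15) / 16.8 − 1.96 = 0.12, giving 55%.

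**6. Sample size does not help.** With all 30 practices and 20 analysed in each, SE is 13.7, and a 15-minute shift gives an error of about 20% instead of 14.5%. A fixed bias weighs more as precision improves.

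These are normal approximations with equal practice sizes. The shift b means whatever remains after any handling of baseline MVPA in the model.

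**The case against.** The strongest reply is that the room for selection is limited:

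- Motivation is one criterion among several, and BMI bands, named comorbidities and failure to meet the activity norm are more objective.
- The criterion concerns willingness to change behaviour, not suitability for a given programme. LSA and dietician contact is the same in both arms, and the Background says that both programmes serve the same kind of patient.
- Participants do not know their practice's allocation.
- MVPA is measured at baseline and the analysis is longitudinal and multilevel, so a shift visible in baseline MVPA may be partly absorbed. The choice of covariates may lie in an analysis plan not shown, so its absence here is no gap.

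All of this stands, and it narrows the concern. It does not answer it: the choice of whom to approach comes before the criteria are applied, and staff discretion is untouched by what patients know. A prognostic difference not captured by baseline MVPA would remain.

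A reader might infer that the arms do differ, or that the bias flatters the supervised programme. The article supports neither. If self-reliant patients were favoured for the light programme and less confident ones for the supervised programme, the bias would run against the supervised arm. With a 15-minute shift in that direction and no true effect, false findings in favour of the supervised programme would fall from 2.5% to about 0.2%. The main harm would then be lost power.

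**Conclusion.** The point holds as a design weakness: at least the ongoing recruitment follows allocation, is run by unblinded staff, and includes a subjective judgement, with no stated safeguard that prevents selective entry. Confidence is high for the recruitment procedure as described and low for its consequences.

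The error rates of about 6% to 32%, and the fall in power from about 84% to about 55% at 15 min/week, show sensitivity to an assumed shift. They do not estimate a bias that the article demonstrates. They rest on the planning SD of 120, intra-cluster correlation of 0.05, 24 practices and 14 completers in each.

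**What to change.** **Remaining recruitment.** Use the same approach rule in every practice, for example one specified record search with patients invited in list order. Log per practice the numbers approached, ineligible (with reason), refused and included. The reach assessment and professionals' registration forms under Process evaluation are a natural base for this log.

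**Analysis.** Adjust the primary multilevel model for baseline MVPA, BMI, age and sex, all listed as baseline characteristics. Add comorbidity and motivation if they were recorded at T0. The article lists motivation as a process item but does not show that it is scored before entry, so this must be confirmed. Compare these variables and the log counts between arms as a recruitment-bias check.

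**What not to do.** Do not introduce a motivation cut-off now. No instrument or threshold is documented, and changing eligibility partway through would create two differently selected cohorts within practices.

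**Cost.** Some practice time for the search and the log. The four core covariates need no new data. Recruitment is planned to last 12 months, so the common rule reaches only patients not yet enrolled. For the others only adjustment and the comparison are available, and adjustment corrects unmeasured selection only in part.

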### Blinding

Although it is not possible to blind the professionals, randomization at the level of GP practices decreases the risk of contamination among the professionals. Participants are not aware of the allocation of their practice to the experimental or control condition.

To identify effects of observer bias, clinical measurements that might be affected (Åstrand test, Valk neuropathy test, body composition, hand grip strength and Timed Up and Go Test) will be repeated by a researcher blinded for the randomization of the practices and the baseline characteristics of the participants. Repeated measurements will be done for 20 participants in five randomly chosen control and five randomly chosen experimental practices.

### Intervention

After inclusion, participants have several consultations with the LSA, dietician and physiotherapist during a one-year intervention period. The number of consultations differs per programme (table 1).

**Table 1 T1:** Contents and number of consultations planned in the control and experimental interventions

Experimental intervention:		Control intervention:	
the 'supervised exercise programme'		the 'start-up exercise programme'	
***Contents of LSA consultations***	***No. of meetings***	***Contents of LSA consultations***	***No. of meetings***
Intake	1	Intake	1
Guidance and follow-up	5	Guidance and follow-up	5

***Contents of dietician consultations ***	***No. of meetings***	***Contents of dietician consultations ***	***No. of meetings***
Intake	1	Intake	1
Guidance and follow-up		Guidance and follow-up	
- Individual	2	- Individual	2
- Group	7	- Group	7

***Contents of physiotherapist consultations***	***No. of meetings***	***Contents of physiotherapist consultations***	***No. of meetings***
Intake	1	Intake	1
Setting up exercise plan	2	Setting up exercise plan	1
Supervised exercise	26 - 34	Follow-up	4
Follow-up	3 - 4		

#### *Experimental intervention ('supervised exercise programme')*

The LSA has a key role in supporting the participants and is the point of contact between the participants and the other health care providers in the 'BeweegKuur' programme. Following an individual intake to set personal goals, participants will have five individual consultations with the LSA to discuss progress in terms of behavioural change, roughly once every 10 weeks, during the one-year intervention period. Consultations with the dietician will consist of nutritional recommendations, education, coping with high-risk situations, checking dietary behaviour and fellow-sufferer contact. Advice will be based on various Dutch guidelines for diabetes, overweight and obesity [25-27]. After an individual intake session by the dietician, seven group sessions are planned. The group meetings comprise guidance and advice by the dietician and are scheduled throughout the year. In addition, two individual follow-up meetings are planned during the intervention period to prevent relapse.

The physiotherapist will provide coaching to enable participants to exercise unsupervised in local exercise facilities. Coaching by the physiotherapist will be initiated by setting out personal goals and identifying barriers hampering engagement in physical activity. Coaching will consist of supervised exercise to overcome any barriers identified and increase physical capacity. Two or three sessions of supervised exercise per week will be planned over a period of 12 weeks. After these 12 weeks, the physiotherapist will evaluate whether the participant is able to exercise without supervision. The coaching period can be extended by four weeks if the participant does not seem able to exercise independently in local facilities. In all, the physiotherapist's coaching will take 12 to 16 weeks. After coaching by the physiotherapist has ended, the five follow-up consultations with the LSA and three or four follow-up consultations with the physiotherapist are planned, to help participants adopt and continue independent exercise activities. Both the LSA and the physiotherapist will help the participant find suitable existing exercise facilities during the entire intervention period.

